## Safety evaluation

9

Safety will be assessed based on adverse events (ADRs) related to the investigational drug, changes in clinical laboratory test results (i.e., hematological screening, clinical biochemical tests, and urine analysis), electrocardiograms (ECGs), and vital signs during the trial period. Possible adverse event items are shown in Table 2.

**Table 2 tab2:** List of possible adverse events.

Systematic organ classification	Adverse events
General	Abdominal pain
	Abscess
	Weakness
	Headache
	Infect
Cardiovascular system	Phlebitis
	Thrombophlebitis
	QTc interval extension
Digestive system	Diarrhea
	Indigestion
	Nausea
	Vomit
	Acute pancreatitis
Blood and lymphatic system	Anemia
	APTT extension
	PT extension
	Thrombocytopenia
	INR elevation
	Hypofibrinogenemia
Metabolism and nutrition	AST elevation
	ALT elevation
	Bilirubin elevation
	Amylase elevation
	ALP elevation
	BUN elevation
	Poor wound healing
	Hypoglycemia
	Hyponatremia
	Hypoalbuminemia
Respiratory system	Pneumonia
Nervous system	Dizziness
Immune system	Allergic/Allergic like Reactions
Skin and accessory structures	Rash
	Pruritus
	Severe skin reactions, including Stevens Johnson syndrome

APTT, activated partial thromboplastin time; PT, prothrombin time; INR, international normalized ratio; AST, aspartate transaminase; ALT, alanine aminotransferase; ALP alkaline phosphatase; BUN, blood urea nitrogen.

Given the documented gastrointestinal toxicity associated with tigecycline, the study protocol will include comprehensive plans for monitoring and documenting specific gastrointestinal adverse events. The Gastrointestinal Symptom Rating Scale (GSRS), a validated tool for assessing gastrointestinal symptoms, will systematically record and rate the severity of gastrointestinal adverse events, including nausea, vomiting, diarrhea, and abdominal pain.

## Data management and monitoring

10

All raw data (Table 3) will be meticulously recorded in the Case Report Form (CRF) by designated researchers. To ensure accuracy, each data entry will be independently double-checked by two individuals. The research coordinator at each center will supervise the data collection process, and the chief investigator, database administrator, and the statistician responsible for the statistical analysis will jointly determine the optimal database location strategy.

**Table 3 tab3:** List of data collection methods.

	Variables
Demographic data	Date of birth, sex, height, weight
Trial characteristics	Dates of screening and enrollment, inclusion criteria and consent details, date and time of randomization
Past medical history and risk factors	Past 3 months’ medical history, concomitant diseases, surgical history, allergic history, medication history (including immunosuppressive drugs, cytotoxic drugs, and biological agents), participation in other drug or medical device clinical trials
Infection and prognostic assessment	cIAI diagnosis time, presumed source of infection, invasive operation for source control, adequacy of source control, residue lesions, ICU admission time, APACHE II score, SOFA score
Antibiotic data	After the onset of the disease, all antibiotic usage, type/time/dose/route/frequency information
Clinical observations	Daily vital signs (blood pressure, heart rate, respiration, body temperature), clinical symptoms and signs, urine output, hematological variables, renal variables, hepatic variables, coagulation function, blood gas analysis, CRP, PCT, use of vasoactive drugs, catecholamine index, use of renal replacement therapy, mechanical ventilation duration, concomitant medication
Microbiological data	Date and time of initial peritoneal drainage culture, full susceptibility profile, daily peritoneal drainage culture results days 1 to 4; any further positive peritoneal drainage cultures and pathogen detection/resistance characteristics; other clinical sites growing *Escherichia*, *Klebsiella* or *Acinetobacter*, any multidrug-resistant organism, *P. aeruginosa* or *Clostridium difficile* identified within 30 days
Outcome data	Survival at 30 days post randomization Date of death or discharge Total response (composite endpoint consisting of clinical cure and microbiological response) at the end of treatment and the test of cure visits Length of ICU stay and costs Protocol violations and adverse events Reasons for trial withdrawal

cIAI, complicated intra-abdominal infection; ICU, intensive care unit; APACHE, Acute Physiology and Chronic Health Evaluation; SOFA, Sequential Organ Failure Assessment; CRP, C-reactive protein; PCT, procalcitonin.

An independent Data Safety and Monitoring Board (DSMB) will be constituted to further enhance the safety and integrity of the study. The DSMB, comprising experts with pertinent knowledge and experience, will operate independently of the study team. Its remit is to conduct regular reviews of the accumulating trial data, to ensure the safety of participants and the validity of the trial results. The DSMB will have the authority to recommend to the sponsor whether to continue, modify, or stop the trial, based on its data review insights.

## Statistics

11

This study is a randomized controlled clinical trial. The two groups are the eravacycline group and the tigecycline group, with a ratio of 1:1. All-cause 30-day mortality is the main outcome measure. The researchers plan to use noninferiority tests for the ratio of two propositions to estimate the required sample size, assuming a noninferiority ratio of 2. Owing to the lack of randomized clinical trials in this specific field, sample size estimates were obtained from Xavier Guirao et al.’s observational study on the treatment of intra-abdominal infections with TGC (16). In their study, the all-cause mortality of patients treated with TGC (our control group) was 18.7%. Our previous results revealed that the mortality rate of the eravacycline group (17.7%) was slightly lower than that of the tigecycline group, with an estimated actual ratio of 0.95. The total sample size calculated through PASS (version 15.0.5) is N = 262 cases to perform a unilateral analysis *α*, achieving 80% efficacy at a level of 0.025. Considering a 10% dropout rate, the total number of subjects required for the last two groups is 292, with at least 146 subjects in each group. In light of the considerable variability observed in ICU mortality rates, an interim analysis will be conducted once 50% of the data has been collected. This analysis will facilitate a reassessment of the effect sizes and power of the study. If the initial mortality rates diverge significantly from the anticipated estimates, the sample size will be adjusted accordingly to ensure the integrity and statistical power of the study are maintained.

The intention to improve treatment will be analyzed based on microbiology, including all randomized subjects, who will be evaluated within their randomized groups. For continuous numerical variables, the quantity, mean, median, standard deviation, minimum, maximum, and coefficient of variation (CV, if applicable) will be determined after an independent sample t test or Wilcoxon rank sum test. The categorical variables will be reported as rates (percentages) and will be analyzed using the Pearson X^2^ test or Fisher’s exact probability method. The baseline will be defined as the last nonmissing observation data collected before the first use of the study drug. The Shapiro–Wilk test and QQ plot in SAS will be used to check the normality of the data. All the statistical analyses will be performed using SAS software (version 9.1 or higher; SAS Institute), and all the statistical inferences will be conducted using a two-sided test with a statistical significance level of 0.05. Confidence intervals (CIs) will be calculated and reported for all endpoints, thereby providing a comprehensive interpretation of the clinical relevance and statistical significance of the findings. Missing data will be classified as response uncertainty, and in the analysis of the microbiological intention-to-treat population, this will be considered treatment failure.

We will calculate and report CIs for all secondary endpoints, such as treatment response rates, to provide a comprehensive interpretation of the clinical relevance and statistical significance of our findings.

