## Population definition

7

The microbiologic modified intention to treat (mITT) population will include all patients with a confirmed diagnosis of complex abdominal infections (cIAIs) and positive infection source samples and/or blood sample cultures at baseline [excluding pathogens not expected to respond to either trial drug, such as nonfermenting gram-negative bacilli (e.g., *P. aeruginosa*, fungi, or mycobacteria)]. The mITT population will be used for demographic and baseline purposes.Clinical evaluation (CE) population: In the mITT population, researchers will follow the requirements of important components of the study protocol [such as cultivating baseline pathogenic gram-negative pathogens (reported in infection source samples and/or blood samples)], excluding those patients with pathogens (*P. aeruginosa*) who do not respond as expected to the investigational drug. This population will be used for clinical efficacy and all-cause mortality analysis.Microbiologically evaluable (ME) population: In the mITT population, individuals who have completed the study in accordance with important components of the study protocol and obtained baseline pathogenic gram-negative pathogens (reported in infection sources and/or blood samples) are expected to respond to the investigational drug. This population will be used for clinical efficacy, microbiological efficacy, comprehensive efficacy, and all-cause mortality analyses.Safety analysis (SS) population: Patients who have received at least one dose of the investigational drug during the clinical study period. The safety analysis population will be used for the analysis of safety data.

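### The 292 enrolled allow only for 10% dropout, so the stated 80% power holds for the clinically and microbiologically evaluable primary populations only if dropout and non-evaluability together stay within 10%

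*Protocol article*

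**What the plan says.** **Sample size (section 11, Statistics).** The calculation is a one-sided non-inferiority test on the ratio of two mortality proportions, "assuming a noninferiority ratio of 2". The control rate comes from an observational study, in which "the all-cause mortality of patients treated with TGC (our control group) was 18.7"%. From the investigators' own earlier results, "the mortality rate of the eravacycline group (17.7%) was slightly lower", "with an estimated actual ratio of 0.95". The result is 262 patients, "achieving 80% efficacy at a level of 0.025". Then: "Considering a 10% dropout rate, the total number of subjects required for the last two groups is 292", or 146 per group.

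**Primary analysis population (Abstract; section 8).** The primary endpoint is 30-day all-cause mortality in the CE and ME populations.

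**Definitions (section 7).** CE and ME are both subsets of the microbiological mITT population, which requires "positive infection source samples and/or blood sample cultures at baseline". As I read the wording, both also require a baseline gram-negative pathogen and adherence to important protocol components. CE removes patients with *P. aeruginosa*. ME needs a pathogen expected to respond, and completion of the study. For CE the section states: "This population will be used for clinical efficacy and all-cause mortality analysis". All-cause mortality is likewise listed among the uses of ME.

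**Entry and conduct.** Section 4.1 does not require a positive culture. Section 6 foresees suspected or isolated *P. aeruginosa* in patients on study.

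**Competing statements.** Section 4.3 announces an intention-to-treat analysis of everyone randomised. Section 11 has a microbiology-based intention-to-treat sentence that also speaks of all randomised subjects.

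**The concern.** A sample size has to be inflated for every route by which a randomised patient can leave the primary analysis. Here the 10% is called a dropout rate in section 11 and a loss rate in the Abstract, and neither place mentions evaluability. The CE and ME definitions add several further routes out: negative culture, no gram-negative pathogen, a pathogen not expected to respond, and protocol deviation. Some of these patients can be enrolled under the protocol's own rules.

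The interim look does not clearly close the gap. Section 11 says that it will reassess effect sizes and power, but the stated trigger for changing the sample size is a divergence in mortality rates. The evaluable share is not named.

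At stake is whether the trial can answer its primary question. An underpowered non-inferiority comparison on mortality may well end inconclusive even if the assumed ratio is true, and readers would have been told to expect 80% power.

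**Working it through.** **Inputs (section 11).** Control mortality p2 = 0.187; true ratio 0.95, so p1 = 0.95 × 0.187 = 0.17765; margin R0 = 2; one-sided α = 0.025; power 80%; allocation 1:1.

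**Step 1: reproduce the plan's figure.** I used the Farrington–Manning score test for a ratio of proportions. Under p1/p2 = 2 the constrained estimate of p1 is the smaller root of 2x² − 3.55165x + 0.7293 = 0.

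- Constrained values: 0.23696 and 0.11848.
- Null variance term: V0 = 0.23696 × 0.76304 + 4 × 0.11848 × 0.88152 = 0.5986, square root 0.7737.
- Alternative variance term: V1 = 0.17765 × 0.82235 + 4 × 0.187 × 0.813 = 0.7542, square root 0.8685.
- n per arm = (1.960 × 0.7737 + 0.8416 × 0.8685)² / (0.17765 − 0.374)² = 130.996, rounded up to 131.

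The total is 262, as stated. Simulating the score test at 262 gives 80.5%.

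**Step 2: reproduce the inflation.** 262 / 0.9 = 291.1, rounded up to 292 for equal arms, as stated. In reverse, 292 × 0.9 = 262.8. After 10% dropout nothing is left for any other exclusion.

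**Step 3: power by number analysed.** With n per arm,

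power = Φ{ (|p1 − 2·p2|·√n − 1.960·√V0) / √V1 }.

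The share of the 292 that reaches CE or ME is an assumption, because the protocol does not give it. Mortality is held at 18.7% and the ratio at 0.95.

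| Analysed | Share of 292 | Power |
|---|---|---|
| 292 | 100% | 84% |
| 262 | 90% | 80% |
| 248 | 85% | 78% |
| 232 | 79% | 75% |
| 204 | 70% | 70% |
| 174 | 60% | 64% |
| 146 | 50% | 57% |

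**Step 4: sensitivity to mortality.** With a ratio margin, power depends strongly on the event rate, and the rate in an evaluable subset need not be 18.7%. With 204 analysed and the ratio still 0.95, power is 60% at 15% control mortality, 70% at 18.7%, 80% at about 22.9% and 84% at 25%. Step 3 is one slice of a wider range.

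**Step 5: two populations.** The primary endpoint names both CE and ME. If non-inferiority must be shown in both, joint power cannot exceed that of the smaller set.

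**The case against.** *The arithmetic is right.* It is. Both 262 and 292 reproduce exactly. A reader might infer a calculation error, but the fault is that the sample-size basis does not match the named analysis populations.

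*The shortfall is not proven.* A reader might infer that the primary analysis will certainly have fewer than 262 patients. The protocol does not support that, because it gives no evaluable share. The Abstract's term loss rate could be meant to cover every kind of loss, and the full protocol behind the article may hold an assumption. What stands is conditional: the 80% requires all losses to fit within 10%, and nothing in the article says that they are expected to.

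*Entry criteria already limit later exclusions.* Section 4.1 refers to pus in the abdominal cavity. Section 4.2 excludes most suspected fungal infection, known resistance to a study drug, and need for additional antibacterials. This makes the 50% and 60% rows speculative, but it does not guarantee a positive gram-negative culture.

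*Culture timing.* One might argue that most patients are randomised before cultures are known. The protocol does not say so. The 24 hours in section 4.1 concern confirmation of infection, and section 4.2 admits some patients whose baseline pathogen is already clear. The point does not need this premise.

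*The trial promises intention to treat.* Sections 4.3 and 11 do refer to all randomised patients, and on that reading 292 is adequate. This is the strongest reply. It conflicts with the Abstract and sections 7 and 8, so it shows a contradiction to be resolved and does not dispose of the point.

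**Conclusion.** The point holds as a conditional one. The protocol's 80% power is correct for 262 analysed patients under its own assumptions, but it has no stated basis for CE and ME, the populations named for the primary endpoint. Power falls below 80% once dropout and non-evaluability together exceed 10% of those randomised, reaches 78% at a 15% loss, and is about 70% at a 30% loss. These figures assume control mortality of 18.7% and a ratio of 0.95 within the evaluable subset. Higher mortality there would offset part of the loss, and lower mortality would deepen it. The absence of an allowance is certain from the text; the size of any shortfall is not. Beneath it lies an unresolved choice between an all-randomised and an evaluable primary population.

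**What to change.** **Preferred.** Reconcile the Abstract and sections 4.3, 7, 8 and 11 by making all randomised patients the primary set for 30-day mortality, with CE and ME as supportive analyses. State power as about 80% with 262 patients and 84% with vital status on all 292, at 18.7% control mortality and a ratio of 0.95. Table 3 (section 10) already lists survival at 30 days after randomisation, so no new data and no extra patients are needed. The cost is an amendment to the primary-population wording in the Abstract and sections 7 and 8, and to the registration, which section 2 says lists the endpoints. In a non-inferiority trial, departures from assigned treatment can pull the arms together in an all-randomised analysis, which is why CE and ME should stay as supportive checks.

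**If CE and ME stay primary.** State the assumed evaluable fraction and its source, and replace the 80% with the power at that fraction, for example about 70% if 70% of those randomised are evaluable. If 80% is to be kept instead, enrolment must rise: 262 / 0.8 = 327.5, so 328 at 80% evaluable; 262 / 0.7 = 374.3, so 376 in equal arms at 70%. Add the evaluable share to what the interim reassessment considers, and correct the intention-to-treat statements in sections 4.3 and 11.

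### The 50% interim may re-size the trial from between-arm effect sizes, while the final test keeps a conventional form at an unadjusted two-sided 0.05; the plan should limit the interim to pooled mortality or name an error-controlling method

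*Protocol article*

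**What the plan says.** The primary endpoint and design are set out in section 11 (Statistics): "All-cause 30-day mortality is the main outcome measure", and "The two groups are the eravacycline group and the tigecycline group, with a ratio of 1:1". The sample size is a noninferiority calculation, "assuming a noninferiority ratio of 2", with control mortality 18.7%, eravacycline mortality 17.7% (ratio 0.95), one-sided 0.025 and 80% power. The result is 262 patients, or 292 after 10% dropout.

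The same paragraph adds an interim analysis at 50% of the data, motivated by variable ICU mortality. Its purpose is given as: "This analysis will facilitate a reassessment of the effect sizes and power of the study". If the early mortality rates differ markedly from those expected, "the sample size will be adjusted accordingly to ensure the integrity and statistical power of the study are maintained".

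Later in section 11 the level is fixed without exception: "all the statistical inferences will be conducted using a two-sided test with a statistical significance level of 0.05". Section 11.1 names the Pearson chi-square or Fisher test for the mortality comparison. No adjusted level, weighted statistic or boundary appears. In section 10, on the monitoring board: "The DSMB will have the authority to recommend to the sponsor whether to continue, modify, or stop the trial".

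**The concern.** An effect size in this trial is a mortality ratio between arms, so reassessing it needs data by arm. The estimates against which the interim rates are compared are arm-specific too. If the second-stage size then depends on the observed ratio, the final statistic no longer has its fixed-sample distribution, and an unadjusted test does not in general hold its level. The stated motive, uncertain ICU mortality, does not need this: overall mortality is a nuisance parameter that can be estimated from pooled data.

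The error at stake is a false claim of noninferiority on death, against a margin that already allows mortality to double.

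This is not just detail left to an unseen analysis plan. The article states an interim that reassesses effect sizes, and it also states one unmodified level for every inference. A later document that controlled the error through an adjusted level or a weighted statistic would contradict sections 11 and 11.1.

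**Working it through.** **Reproducing the planned size.** Inputs from section 11: p2 = 0.187, p1 = 0.95 × 0.187 = 0.17765, R0 = 2, one-sided 0.025 (z = 1.960), power 80% (z = 0.842), 1:1.

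Farrington-Manning formula per arm: n = [1.960·√V0 + 0.842·√V1]² / (p1 − R0·p2)².

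- Rates restricted to ratio 2: q1 = 0.2370, q2 = 0.1185.
- V0 = q1(1 − q1) + 4·q2(1 − q2) = 0.1808 + 0.4178 = 0.5986.
- V1 = p1(1 − p1) + 4·p2(1 − p2) = 0.1461 + 0.6081 = 0.7542.
- Denominator: (0.17765 − 0.374)² = 0.03855.
- n = (1.5164 + 0.7309)² / 0.03855 = 5.050 / 0.03855 ≈ 131 per arm, 262 in total.
- Dropout: 262 / 0.9 = 291.1, so 292 in two equal arms.

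Both stated figures reproduce. Neither contains an allowance for the interim.

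**Type I error.** 600,000 simulated trials per scenario at the null boundary (37.4% versus 18.7%, ratio 2), with the interim at 66 per arm and N recalculated by the formula above for 80% power. The final test is a Farrington-Manning test of ratio 2 at one-sided 0.025, which is the same nominal level as two-sided 0.05. That test, the caps and the re-estimation rules are assumptions, because the article gives no rule and names only Pearson or Fisher.

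| Rule for N | One-sided error |
|---|---|
| Fixed, 131 per arm | 2.7% |
| Observed arm rates, increase only, cap 1.5× | 3.0% |
| Observed arm rates, increase only, cap 2× to 4× | 3.2–3.5% |
| Observed arm rates, may also fall, cap 1.5× | 3.4% |
| Observed arm rates, may also fall, cap 2× to 4× | 3.6–3.9% |
| Blinded pooled rate, ratio 0.95 and margin 2 fixed | 2.7–2.8% |

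Control mortality of 12% or 25% gives similar results (3.0–4.0% with observed rates). Moving the interim to 73 per arm also changes little; the blinded rule is then about 2.75% with increases only and 2.9% if N may fall as well. About 0.2 points of the excess over 2.5% belong to the test itself. Against 2.7%, effect-based re-estimation adds about 0.5–0.8 points (3.2–3.5%) or 0.9–1.2 points (3.6–3.9%).

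**Stability of an effect-based N.** With 73 per arm, expected deaths under the planning rates are 73 × (0.187 + 0.17765) ≈ 27. For an observed ratio of 0.95, the standard error of the log ratio is √[0.82235/(73 × 0.17765) + 0.813/(73 × 0.187)] = √(0.0634 + 0.0596) = 0.351. The 95% interval is 0.95 × exp(±1.96 × 0.351), about 0.48 to 1.89. An N computed from such a ratio would be erratic.

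**The case against.** The strongest reply is that section 11 keeps two things apart. Effect sizes and power are reassessed, but the trigger for changing N is a departure of mortality rates, the motive is variable ICU mortality, and the aim is to preserve power. On that reading only a nuisance rate is checked. Section 5 supports it to a degree, since the researchers who analyse the data are to be kept unaware of the groups, and section 10 makes the monitoring board independent. Who sees arm-level data, and under which cap, is detail that a condensed article may leave out.

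Much of this stands. The article does not say that N is computed from the observed ratio, that N may fall, or that the interim is unblinded. Nor does every rule that uses the observed effect inflate the error: raising N only when conditional power is at least 50% gave 2.6% in simulation. Using the control-arm rate alone with the ratio fixed, increases only, gave 2.8% at 18.7% control mortality.

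It does not remove the point. The article names effect sizes as an object of the interim, its reference values are arm-specific, and masking the analysts does not prevent a comparison under coded labels. The reading that inflates the error is open on the text, and the final level and test are fixed as if no adaptation had taken place.

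**Conclusion.** The concern holds in conditional form. If N is recalculated from the observed arm-specific rates and the final test stays as written, the one-sided error at ratio 2 is about 3.2–3.5% (increase only) or 3.6–3.9% (either direction), against about 2.7% with fixed N. If only pooled mortality is used, there is no material inflation. These figures rest on the assumed Farrington-Manning test, caps of 2 to 4 times and recalculation for 80% power.

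A reader might infer two stronger claims that the article does not support:

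- **That the false noninferiority rate certainly exceeds its declared level because of the interim.** This depends on a rule that is not given.
- **That the error reaches 5–6%.** Figures just above 5% need the interim to serve also as an unadjusted success test, and no efficacy test is stated; the board's remit to recommend stopping is general. The bound 0.025 + exp(−1.96²/2)/4 = 0.025 + 0.0366 = 0.0616 applies to the worst possible rule with no limit on N.

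The inflation is moderate, but it cannot be repaired credibly once arm-level results have shaped N. The text should therefore be settled before the interim.

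**What to change.** **Preferred.** Amend the interim paragraph of section 11 so that, at 50% of 30-day outcomes, only the blinded pooled mortality m is computed. Keep ratio 0.95 and margin 2 fixed, take control mortality as 2m/1.95, and recalculate N with the planning formula. Allow increases only, up to a stated cap, and make no between-arm efficacy comparison. Remove effect sizes from the stated purpose. The final one-sided 0.025 (two-sided 0.05) can then stand, to the accuracy of the test itself.

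For setting the cap, the planning formula with ratio 0.95 gives totals before dropout of 342, 442 and 540 at control mortality of 15%, 12% and 10%. A cap of 2 × 262 = 524 would cover 12% but not 10%.

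**Alternative.** If effect-based re-estimation is intended, prespecify a combination or weighted test. If an efficacy look is intended, prespecify a group-sequential boundary. For one look at half the information with the final size unchanged, O'Brien-Fleming uses two-sided 0.0052 and then 0.0480, and Pocock uses 0.0294 at both looks. Either choice requires the level in section 11 and the test in section 11.1 to be amended to match.

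**Cost.** One paragraph. The small downside of the blinded option is that N cannot be re-tuned to the observed treatment effect; the alternative keeps that freedom at the price of a more complex final analysis.
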